#### Spatial analyses

Spatial analyses will be carried out to study the extent to which cases of dengue are spatially differentiated, and assess predictors that could explain these differences. We will use local methods of aggregates detection in space. The spatial scan approach elaborated by Kulldorf [74] will be adapted for our purpose. Typically, the scan statistic is used to identify unusual clustering of cases, but we will capitalize on its properties to determine whether any observed spatial heterogeneity is due to a few distant spatial units or to larger geographic zones of varying risk [75]. Geographically weighted regressions [76] will enable understanding the relation between the outcomes of primary interest: IgG seroconversion and adult female *Aedes* density, while cluster analysis using Local Indicators of Spatial Association [77] will allow us to assess of the significant of spatially-concentrated cases. We will examine various environmental and population-level demographic spatial predictors that could explain the spatial heterogeneity of dengue transmission risk using a Bayesian hierarchical Poisson model.

#### Missing data

There will likely be in-migration and out-migration from the community and we will add new arrivals to the study (but will not follow those leaving the household clusters if they move outside of a study cluster). We do not expect there to be differential out-migration between intervention and control clusters. To decrease the potential selection bias resulting from informative censoring (differential attrition) we will 1) minimize loss to follow-up by performing home-based visits, and 2) at the analysis stage, make use of methodological techniques such as inverse probability of censoring weighting [78, 79], which enables estimation of the effect in the presence of informative censoring by weighting each participant according to their conditional probabilities of staying or leaving the study [80]. In addition, it has been shown that the participatory approach of community-based interventions enhances the participation and reduces the attrition in health interventions [7, 81, 82]. In any case, attrition will be reported and managed adequately to best standards for RCT validity [83]. We will analyse missing data using Amelia II [84] to impute values for missing data for the primary outcome (serological evidence of recent DENV infection). Estimates will reconcile data from ten imputed cross-sectional data sets in the R package Zelig [85] applied at multiple time points.

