### Trial design

We will follow a parallel pragmatic cluster randomized controlled trial (cRCT) design with randomization at the census tract level with equal allocation to the two arms, to evaluate the effectiveness of community mobilization measured by the risk of primary DENV infection, self-reported dengue cases, and *Aedes* infestation rates. The quantitative baseline assessment will include a household questionnaire, entomological evaluation of households and high-risk communal areas, and blood samples (from finger pricks) from children aged 3–9 years. Following the baseline assessment, allocation will occur after which community mobilization activities will begin for a period of 24 months. Baseline community interviews and focus groups for the qualitative studies will be performed just after allocation.

This is an investigator-initiated trial that was registered with ISRCTN66131315 prior to enrollment. The trial protocol was developed according to the Standardized Protocol Items: Recommendations for Interventional Trials (SPIRIT) guidelines (Additional file 1) [35].

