#### Recruitment

Based on preliminary and exploratory studies [7, 8, 45, 53, 54], we observed high participation rates in seroprevalence surveys (93% to 100%) and the finger prick in children to collect blood samples was well accepted [45, 53–56]. During door-to-door enrolment visits the research teams will be assisted by community workers and volunteer facilitators to explain the aim and importance of the research to families. The starting point of household recruitment will be the centroid (as determined by QGIS) of each selected cluster with a radial pattern of household recruitment from the starting point, following the pattern of city blocks within the cluster.

Eligibility criteria of the household and individual will be verified. The goals of the study and all procedures will be detailed following a pre-established script, the consent forms will be explained, and we will allocate adequate time to answer any prospective participant questions. Immediately after enrolment and consent of participation, entomological data collection and/or blood collection, as well as questionnaires administration will occur.

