#### Blinding

Study participants will be aware of their assignment given that active participation in research design and activities will be encouraged for participants in the intervention group, whereas participation of those in the control group will not be solicited. Research staff involved in data collection will be blind to intervention assignment although intervention assignment may be revealed through interaction with the participants. During the analysis, all data will be anonymized, and research staff involved will be blinded to group assignment.

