### Statistical methods

We will follow an intention-to-treat (ITT) approach. To estimate the potential impact of the intervention on the risk of dengue seroconversion, we propose a conditional (multilevel) modeling approach (i.e., using mixed effects models) [69]. To estimate the incidence risk ratio of seroconversion in the intervention group relative to the control group, a log-binomial model will be used which assumes a log link under the assumption of a binomial distribution [70]. Since the intervention effect of marginal and conditional models are only the same for the identity and log links [69], if convergence is an issue, a robust Poisson model with log link and robust variance will be used [70]. In addition to the fixed effect for the intervention, the log-binomial mixed model will have random effects for strata, measurement period (baseline, first follow-up, second follow-up), household, and census tract (cluster). The random effects for period will allow us to assess period by period differences in the risk of seroconversion. Also, as an alternative to the strata random effects, we will consider the baseline risk indicator (cumulative dengue incidence at the bairro level) that was used to stratify clusters. Additional baseline covariates may be considered for inclusion at the patient and household level (e.g., age, sex, socioeconomic status). We anticipate that the cluster sizes will remain relatively similar across all clusters but if losses due to attrition result in significant differences, we will then use inverse probability weights by cluster size in the analysis. For the primary outcomes of adult female *Aedes* density, we will use the same approach: a conditional (multilevel) modeling approach (i.e., using mixed effects models) with a Poisson distribution. For KAP and social capital, they will be examined as potential effect modifiers/confounders with each outcome. An index of KAP will be created using principal component analysis. Additionally, indicators on the community interventions captured from the fidelity analysis (e.g., content, coverage, frequency, and duration) may be included as fixed effects in the models to estimate the impact of intervention variability on the results.

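### New arrivals may join after allocation with no limit on entry to the primary seroconversion analysis, which risks post-randomisation recruitment bias

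*Protocol article*

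**What the plan says.** The Missing data section expects movement in both directions. On people moving in it states "we will add new arrivals to the study"; on people moving out, the team "will not follow those leaving the household clusters if they move outside of a study cluster". It gives no closing date for arrivals, no minimum residence, and no rule on which analyses they enter. For informative censoring it proposes inverse probability weights built on the probability of remaining in or leaving the study.

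The Trial design section fixes the order of events: "Following the baseline assessment, allocation will occur after which community mobilization activities will begin for a period of 24 months". The Allocation section places randomisation after both baseline collections.

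The Blinding section says "Study participants will be aware of their assignment given that active participation in research design and activities will be encouraged" in the intervention group, and that control participation is not sought. Data collectors are nominally blind, but "intervention assignment may be revealed through interaction with the participants"; the Abstract calls this likely for field staff. Under Recruitment, during door-to-door enrolment "the research teams will be assisted by community workers and volunteer facilitators".

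Statistical methods opens with "We will follow an intention-to-treat (ITT) approach" and says nothing about children who join after allocation.

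**The concern.** In a cluster trial, randomisation balances the people who were in the clusters and enrolled when the arms were assigned. Completing baseline enrolment before allocation, as this trial does, keeps knowledge of the arm out of the decision to join. An open door after allocation gives that protection up for whoever enters later.

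Several features make the risk more than theoretical here. Families know their arm. Engagement is sought in one arm only. Community volunteers act as organisers and educators in intervention clusters (Intervention section), and volunteer facilitators assist enrolment. If arrivals are enrolled in the same way, people who deliver the intervention may help to recruit. The Missing data section itself argues that participatory approaches raise participation and lower attrition; only one arm receives the participatory approach, so by the protocol's own reasoning willingness to join could differ by arm.

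At stake is a difference in seroconversion that reflects who joined and not what the intervention did. Its direction cannot be known in advance.

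**Working it through.** **1. Does entry after allocation follow from the text?** The Missing data section gives no timing. Enrolment and both baselines come first, then allocation, then 24 months of activity. Trial status has recruitment complete by 30 June 2020. Some families could move in between the dry-season and rainy-season baselines and so join before allocation. Arrival during follow-up is the more natural meaning, and nothing limits arrivals to the earlier window.

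**2. Does another provision remove the problem?** The weights model exit, not entry. Multiple imputation fills in missing outcomes and does not correct for who was recruited. Period effects in the model can absorb calendar differences, but not selection into the study. No passage restricts the primary analysis to the pre-allocation cohort.

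**3. Does the sample size need arrivals?** Inputs from the Sample size section: risks 0.30 and 0.2115, ICC 0.07, 60 children per cluster, 80% power, significance level 0.05 (taken as two-sided).
- Design effect: 1 + (60 − 1) × 0.07 = 5.13.
- Children per arm before clustering, normal approximation: 381 (pooled variance) or 377.6 (unpooled).
- Clusters per arm: 381 × 5.13 / 60 = 32.6, or 377.6 × 5.13 / 60 = 32.3, against the stated 32.
- Power at 32 clusters: 0.794 (pooled) or 0.797 (unpooled), against the stated 0.80.
- Attrition: 60 / 0.7 = 85.7, rounded up to 86; 86 × 68 = 5848.

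The protocol's figures are reproduced to within rounding. They describe a closed cohort that loses 30% and is not topped up. Power therefore stays at about 0.79 to 0.80 with no arrivals in the primary analysis.

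**4. How large could recruitment bias be?** Two inputs are assumptions, because the documents give neither: the share f of analysed children who are arrivals (10% to 30%), and the risk ratio r of intervention-arm to control-arm arrivals arising from selection alone. With no true effect, the apparent risk ratio is 1 − f(1 − r). The intervention-arm risk is 0.30 times that value. The effective number per arm is 32 × 60 / 5.13 = 374.3. The rejection rate comes from the two-sided unpooled z-test at 0.05.

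| f | RR, r = 0.8 | Rejection | RR, r = 0.7 | Rejection |
|---|---|---|---|---|
| 10% | 0.98 | 5.4% | 0.97 | 5.8% |
| 20% | 0.96 | 6.5% | 0.94 | 8.4% |
| 30% | 0.94 | 8.4% | 0.91 | 12.9% |

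For example, f = 0.3 and r = 0.8 give 1 − 0.3 × 0.2 = 0.94, an intervention-arm risk of 0.282.

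**5. Is there a loss of power from partial exposure?** The answer changes with the assumption (32 clusters, ICC 0.07, pooled variance):
- Arrivals take places within the 60 and get half the relative reduction. The overall reduction is 29.5% × (1 − 0.5f), that is 28.0%, 26.6% and 25.1% at f = 10%, 20% and 30%. Power is 0.75, 0.70 and 0.65.
- Arrivals come on top of the 60, so cluster size is 60 / (1 − f), and get half the reduction. Power is 0.757, 0.716 and 0.673.
- Arrivals come on top of the 60 and get the full reduction. Power is 0.801, 0.808 and 0.815.

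The documents do not favour any of these, so no loss of power can be claimed.

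**The case against.** The article says that arrivals join the study; it does not say that they enter the primary seroconversion analysis. Mosquito density, container index, premise condition, KAP and self-reported dengue are also measured, and current residents are a natural population for those. Detail on analysis sets is often left to a fuller document. This stands in part: entry into the primary analysis is an inference. But the article does more than stay silent. It opens the cohort, declares intention-to-treat and states no limit, so a team following it as written could include arrivals.

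A reader might infer that partly exposed children breach intention-to-treat. They do not. Analysing residents in their cluster's assigned arm is a legitimate open-cohort approach in a pragmatic trial. A reader might also infer diluted power. The intervention acts on breeding sites across the cluster, so a child observed from their own first sample may receive much of the effect, and step 5 shows that power can even rise slightly.

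The upper share of 30% may be generous. An arrival contributes to seroconversion only with a negative first sample and a later one. On the schedule of baseline and two follow-ups in Statistical methods, a child first sampled at the last round contributes nothing. The outcome is a laboratory ELISA and analysts are blinded. That limits bias in measurement, but not bias in who is recruited.

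**Conclusion.** The concern holds as a risk. Nothing in the article keeps children recruited after allocation out of the primary seroconversion comparison, and nothing planned corrects for recruitment that differs by arm. It would be too strong to say that bias will occur, that the trial is unblinded throughout (participants know their arm; data collectors are nominally blind), or that intention-to-treat is violated.

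The size is unknown. Under the assumed selection ratio of 0.8 it is close to negligible at a 10% share (apparent risk ratio 0.98, rejection 5.4%) and noticeable at 30% (0.94, rejection 8.4%). Both the share and the ratio are assumptions. The change is worth making because the risk can be avoided at almost no cost.

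**What to change.** Define the primary seroconversion analysis as children enrolled and sampled before allocation, analysed by their cluster's assigned arm. Report the number of new arrivals by arm and date of entry. Include them only in an open-cohort sensitivity analysis, with risk time starting at each child's own first sample.

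This takes one or two sentences and no extra recruitment. There are two costs: slightly fewer children in the primary analysis, and a primary result that describes the baseline cohort and not all current residents. The sensitivity analysis covers the second.

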### Qualitative methods

#### Fidelity and process analysis

We will first incorporate feedback on the intervention’s theory of change from key stakeholders. To measure fidelity, programmed activities (defined with specific descriptors using questions formulated based on the theory of the intervention) and their actual implementation will be compared in terms of content, coverage, frequency, and duration [86]. The assessment of processes will focus on the internal dynamics of the interventions, the roles, perceptions and coping strategies of actors, adaptation to changes brought about by activities, implementation fidelity moderating factors (i.e. quality of delivery of the intervention, participants recruitment, responsiveness/acceptability and expectations, comprehensiveness of the intervention description, facilitations strategies and implementation context), barriers and facilitators of the implementation, any unintended effects, the evolution of programs and activities, and the mediating effect of the context [87–89]. Data will be collected from the self-report forms established for process documentation and from in-depth interviews with a purposive heterogeneous sample of implementation from key stakeholders. We will assess the participation process using a participation framework and indicators [90, 91]. The fidelity data will be analysed with the Perez et al. [46] framework and qualitative data will be analysed using an inductive approach [92]. Component analysis will be also conducted by using implementation fidelity data and outcomes performance from different implementation units of the intervention.

#### Social acceptability analysis

This analysis will be performed on two levels with a mixed methods approach using the theoretical framework proposed by Sekhon et al. [65]. The acceptability of stakeholders involved in designing and implementing the interventions will be assessed in the development and adaptive process of the activities. The qualitative data will be collected through the in-depth interviews planned for assessed fidelity moderators mentioned above. Acceptability will also be assessed with quantitative data at household level as part of the household surveys. The qualitative data will be analysed using a framework analysis approach [92, 93] and the household survey data will be analysed using a generalized estimating equation approach for proportional odds logistic regression model with repeated measures [94].

#### Realist analysis

Realist evaluation (RE) [67] is an innovative approach to understand complex social interventions such as community mobilization. Using generative causation, RE aims to highlight cause-and-effect tendencies in the occurrence of an outcome in a specific context by determining the reasoning and reactions of agent(s) [95]. RE will focus on: i) participation of stakeholders; ii) adaptation of interventions; and iii) education and awareness of target populations. An embedded multiple-case study design will be used [96], with the three entities of analysis. These will include participants, neighbourhoods, and households. First, we will develop concrete theories underlying the potential effects of specific programme mechanisms through a workshop involving key stakeholders. Second, the research team will generate hypotheses from the theoretical literature to explain the process by which the intervention may produce the outcomes in certain contexts. Third, the hypotheses will be tested on empirical data, in order to clarify interactions between contexts, mechanisms and outcomes. Empirical data will be provided by the same focus group and individual interviews with communities in addition of individual interviews with key stakeholders involved in the intervention implementation, as well as the results of the KAP questions from the household survey.

#### Sustainability analysis

A planned and regular documentation of the project using the Template for Intervention Description and Replication for Population and Health Interventions [97], as well as in-depth interview with key players of the intervention, and cost data will help us evaluate the potential for sustainability of the intervention. We will use the five programmatic characteristics (leadership, capacity, interactions (notions of integration), flexibility/adaptability and performance) proposed by Shigayeva and Coker (2015) [98] to perform this analysis. The qualitative data will be analysed using a framework analysis approach [93].

### Methods: monitoring

#### Data monitoring

An external data monitoring committee will not be appointed given the low-risk to participant safety, although there will be an internal Data & Technology committee that will manage the data monitoring and evaluation for data quality assurance. Data monitoring will occur in real-time to examine response rates and numbers of interviews, missingness and other data quality issues, location match checking, and to identify problematic questions or interviewers. Data will be analyzed immediately after the baseline survey to disseminate the results during the needs assessment. Following this, the quantitative and qualitative data will be analyzed every 6 months following data collection for preliminary results with a global analysis at the end of follow-up. The results of the dengue incidence testing in study participants will be reported to Epidemiology Surveillance Division of the Fortaleza Municipal Health Secretariat.

#### Harms

The nurses who will be conducted the finger pricks, will be encouraged to report any potential adverse events (e.g., haemolysis, severe pain) to the investigators, who will report these findings to the governing institutional review boards [99].

### Ethics and dissemination

#### Consent

Consent forms will be presented and the study explained to household principal respondents to obtain the authorization of the household participation, using a standard script. They will explain that participants may decline to answer any questions and may terminate the interview at any time, which will proceed if the respondents have provided their consent. An additional consent form will be presented and explained to the parent or legal guardian of the eligible child, to obtain blood samples via finger pricks, with the assurance that the results will be returned to them. The study and the procedure for blood collection will also be explained to the child in an age adapted language, who will be asked for study participation acceptance using an assent form, which may include the use of visual aids.

#### Confidentiality

Maintaining confidentiality of participants and communities will be central to the training of fieldworkers and data operators. Only group findings will be reported with no names or personal identifiers recorded next to individual responses. All surveys and laboratory specimens will be identified by a coded ID, which will be used to link households and children participants to their information. All records that contain names or other personal identifiers will be stored separately and will have restrict access: paper informed consent will be stored under key at the Universidade Estadual do Ceará, and coded IDs file in a password protected database. These data will be kept for 7 years after the end of the project (December 2029). Anonymized data will be safely stored in a backup platform of the Institut de recherche pour le development (IRD), France, and protected by secure access. In focus groups, no names of focus group participants will be recorded, and reports of focus group findings will not identify individual communities. All principal investigators will be given access to the cleaned, final datasets.

